### Blinding

Blinding of the general practitioners regarding group identity is not possible. Patients do only know that different types of blood pressure record booklets are being distributed, but they do not know in detail what the difference between the booklets is.

#### Intervention

The patients in the intervention group will receive a colour-coded blood pressure record booklet. The corresponding colour coded areas are divided into three areas of green, yellow and red following a traffic light system. The green area covers blood pressure readings up to a maximum of 140/90 mmHg, the yellow area includes systolic readings over 140 to 180 mmHg and diastolic readings over 90 to10 mmHg. The red area covers systolic readings over 180 mmHg and diastolic readings over 110 mmHg. All patients will be trained in the standardised use of the blood pressure record booklet including home blood pressure measurement additional they receive an instruction leaflet. They will be asked to measure their blood pressure in the morning while they are sitting and before they take their blood pressure medicaments. The readings will be recorded in the relevant blood pressure booklet for six months. All patients will be trained in the same way for one of the two study BP booklets by the general practitioner or the practice assistant for the duration of the study. The general practitioners and practice assistants will receive the same instruction and training for this as well as an instruction leaflet. Validated electronically blood pressure meters (MioStar Cardioplus 500) will be provided to all practices and patients to assure a standardization of the measurement. All measurements have to be performed with these meters.

### Data collection

#### Primary end point

There will be blood pressure measurements by the general practitioner at the start (t0) as well as after 3 months (t1) and at the end of the study after 6 months (t2). To rule out blood pressure differences BP will be measured at both arms at t0. Each subsequent measurement in the practice of the general practitioner will involve two blood pressure measurements in each case in the left arm if the initial measurement did not differ between both arms by more than 5 mm Hg. If the measurement differed by more than 5 mm Hg at t0, BP will be measured at the arm with the higher reading subsequently. All the readings will be recorded, but for inclusion (as stated above) as ell as for analysis, the second measurement will be used. The difference (t2-t0) between the systolic blood pressure readings at the practice measurement represents the primary end point.

All patient contacts will be collected over the entire period. At time t2 (after the end of the study) the number of times there was contact with the general practitioner since the inclusion of the patient will be recorded.

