### Inclusion criteria for patients

• Age >18 years

• BP > 140/90 mmHg

Two consecutive measurements carried out in the practice

(measured by the general practitioner or practice assistant at the start of the study; both measurements must be greater that 140/90 mmHg with the second measurement qualifying for inclusion.

• Unchanged anti-hypertension treatment for one month before inclusion

• Patient able to measure blood pressure at home

• Written informed consent

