#### Analysis

At the end of the study the list with the booklet codes as well as the code, generated out of the patients' name and his birthday will be send to the study centre. In the study centre, all received questionnaires and lists will be scanned electronically and a TIF-file will be generated to avoid data manipulation. The data will be directly exported in the statistic program (STATA, version 9).

Descriptive statistics: average value with +/- 1 SD and median values of the average blood pressure readings for both groups. In accordance with the normal distribution test it will be decided whether parametric or non-parametric tests are to be applied. Treatment group comparisons for categorical data will be done with the χ^2 ^test. For continuous variables, comparisons between treatment groups were done with *t *tests.

Primary outcome: difference (t2-t0) between the systolic blood pressure average readings from the practice measurement. All patients will be analysed in accordance with the „intention-to-treat” approach and the latest available measurement will be used (last- observation carried forward). When interventions are provided via GPs, one should be aware of a cluster effect. We decided to perform a randomisation on the patient's level since the effect mediated by the GP on the intervention is assumed to be small. Nevertheless, we will account for that and include the factor "Practice" as a random effect in the analysis.

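### The primary comparison of change in systolic BP names no baseline covariate: it is valid, but it fixes the baseline coefficient at 1 and gives up precision that costs nothing to recover

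*Protocol article*

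**What the plan says.** The section Primary end point defines the outcome: "The difference (t2-t0) between the systolic blood pressure readings at the practice measurement represents the primary end point". Practice BP is taken at t0, 3 months (t1) and 6 months (t2). Two readings are taken at each practice measurement after t0, and "for analysis, the second measurement will be used".

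The Analysis section repeats the outcome: "Primary outcome: difference (t2-t0) between the systolic blood pressure average readings from the practice measurement". On method it says: "For continuous variables, comparisons between treatment groups were done with" t tests, with non-parametric tests as the alternative if a normality test so indicates. The authors also undertake to "include the factor 'Practice' as a random effect in the analysis". Baseline systolic BP is not named as a covariate anywhere.

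On entry, the Inclusion criteria for patients state: "both measurements must be greater that 140/90 mmHg with the second measurement qualifying for inclusion". The Exclusion criteria cap systolic BP at 180 mmHg. The second t0 reading therefore both admits the patient and is subtracted in the end point.

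**The concern.** A change score corrects for baseline, but with a slope that is assumed, not estimated: each mmHg of difference at t0 is taken to carry through in full to t2. When patients are admitted because a noisy reading exceeded a threshold, part of that reading is transient, and the slope of t2 on t0 will ordinarily be below 1. Two consequences follow.

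- **Precision.** The variance contains a term that a baseline-adjusted model would remove.
- **Conditional bias.** If one arm starts higher by chance, it shows a larger fall with no booklet effect. Randomisation balances this over repeated trials but not in the one trial that is run.

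What is at stake is efficiency, and the credibility of the estimate if the arms happen to differ at t0. Naming the covariate in advance also prevents a later choice between adjusted and unadjusted results.

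**Working it through.** **Inputs from the article (Sample Size).** Difference 7 mmHg, SD 14 mmHg, one-sided alpha 0.05, power 0.90, total 138. The article does not say whether 14 is the SD of the change or of a single reading. Equal allocation is assumed.

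**The plan's own figure.** n per arm = 2(1.645 + 1.282)² × 14²/7² = 68.5, so 69 per arm and 138 in total. This reproduces exactly, with power 90.2% at 138.

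**General relation.** Let s0 and s2 be the SDs at t0 and t2, r their correlation, and b = r·s2/s0 the slope of t2 on t0.
- Var(change) = s0² + s2² − 2r·s0·s2
- Var(adjusted) = s2²(1 − r²)
- The difference is s0²(1 − b)². It is never negative and is zero only at b = 1. This ignores the small cost of estimating b.

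**Case A: equal SDs, with 14 as the SD of the change.** The variance ratio (adjusted to change) is (1 + r)/2.

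| r (assumed) | Ratio | Residual SD | N for 90% power | Power at 138 |
|---|---|---|---|---|
| change score | 1 | 14.0 | 138 | 90.2% |
| 0.3 | 0.65 | 11.3 | 90 | 97.7% |
| 0.5 | 0.75 | 12.1 | 104 | 96.0% |
| 0.7 | 0.85 | 12.9 | 118 | 93.8% |
| 0.8 | 0.90 | 13.3 | 124 | 92.7% |

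**Case B: equal SDs, with 14 as the SD of a single reading.** For r = 0.3 / 0.5 / 0.7 / 0.8, the change score needs N = 192 / 138 / 84 / 56 and the adjusted analysis 126 / 104 / 70 / 50. At r = 0.3, power at 138 is 80% for the change score and 92% adjusted.

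**Case C: baseline spread narrowed by the entry limits.** With assumed SDs of 10 at t0 and 14 at t2, and r = 0.3 / 0.5 / 0.7, the slope is 0.42 / 0.70 / 0.98 and the ratio 0.84 / 0.94 / 1.00. The gain can therefore vanish.

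**Case D: simulation of the entry rule.** Assumptions: systolic mean 145, between-patient SD 12, within-patient SD 9 or 12, independent reading errors, both t0 readings above 140 and none above 180, second reading as baseline, no treatment effect, diastolic BP ignored.

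| Within-patient SD | s0 | s2 | r | Slope b | Ratio | Mean change, each arm |
|---|---|---|---|---|---|---|
| 9 | 9.3 | 12.2 | 0.41 | 0.53 | 0.87 | −2.1 mmHg |
| 12 | 9.9 | 14.8 | 0.27 | 0.41 | 0.86 | −3.5 mmHg |

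Applying these ratios to an SD of change of 14 gives residual SDs of about 13.1 and 13.0, and power at 138 of 93.4% and 93.6%, against 90.2%. If the errors of the two consecutive readings are strongly correlated, the rule acts more like selection on one reading. The same inputs then give ratios of about 0.92 and 0.90.

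**Chance imbalance.** A t0 difference d shifts the change-score contrast by (1 − b)d, in favour of the arm that starts higher. In case D, one standard error of d at 69 per arm is 9.3 × √(2/69) = 1.6 or 9.9 × √(2/69) = 1.7 mmHg, so 1 to 2 mmHg is ordinary. For d = 2, the shift is 2(1 − 0.53) = 0.9 or 2(1 − 0.41) = 1.2 mmHg, or 13% to 17% of the 7 mmHg target.

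**The case against.** The strongest reply is that nothing here is an error. Allocation is at patient level, a change score is a conventional end point, its comparison between arms is unbiased with correct type I error, and the sample size reproduces from its own inputs without relying on a precision gain. The t-test sentence is generic, the article does not say that practice is the only model term, and an analysis plan not shown could add baseline. All of that stands. It limits the point to a recommendation but does not remove it, because the article does name its test and one adjustment factor, and baseline is not among them.

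Four stronger readings are tempting, and the document does not support them.

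- A reader might infer that baseline imbalance is left uncorrected. It is corrected, with a coefficient of 1; where the slope is below 1, that is too much.
- A reader might infer that regression to the mean from the entry rule biases the trial. It occurs in both arms and cancels on average in the randomised contrast. Only the part tied to a chance difference at t0 remains, and it can favour either arm.
- A reader might infer that the end point should be replaced. With t0 as covariate, modelling t2 − t0 or t2 gives the same treatment estimate, so the gap lies in the Analysis section.
- A reader might take the gain of about 6 points in power at r = 0.5 as the expected benefit. It requires that correlation, equal SDs at t0 and t2, and 14 as the SD of the change. The article states none of these, and the entry limits restrict t0 but not t2, which makes equal SDs doubtful.

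**Conclusion.** The point holds as a matter of efficiency and conditional bias, not validity. The Analysis section fixes a comparison of change that names no baseline covariate, while t0 is available for everyone and is the reading on which patients were selected. Adjusting is, in large samples, at least as precise, and it removes the over-correction of chance imbalance.

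The size is uncertain. The most relevant assumed case, the simulated entry rule, gives a variance reduction of about 13% to 14%, or roughly 3 points of power if 14 is the SD of the change. The range runs from 35% (equal SDs, r = 0.3) to almost nothing when the slope is near 1. The correlation, the SDs at t0 and t2, and the meaning of the SD of 14 are all absent from the article. The change is worth making because it is free, not because the stated analysis would mislead on average.

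**What to change.** Keep t2 − t0 systolic BP as the end point. In the Analysis section, state the primary analysis as a linear mixed model of t2 − t0 (or, equivalently, t2) systolic BP, with arm and t0 systolic BP as fixed effects and practice as a random effect. The t0 covariate should be the same reading that enters the change. Report the adjusted mean difference with its confidence interval as the primary result and the unadjusted change as supportive. In Sample Size, say whether the SD of 14 mmHg refers to the change or to a single reading. If a separate analysis plan already adjusts for baseline, align the protocol text with it.

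The cost is wording only: t0 is already collected, and no patients, visits or measurements are added. The change should be made before outcome data are examined by arm.

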### Secondary end point

- Number of patients, who achieve blood pressure control under 140/90 mm Hg.

- Adherence: the absolute number of blood pressure measurements (entries in the BP record booklet) by the patients will be assessed as correlative of adherence during the period of observation.

The first supply of data takes place at randomisation and subsequent at the specific measuring points t1 and t2.

#### Analysis

At the end of the study the list with the booklet codes as well as the code, generated out of the patients' name and his birthday will be send to the study centre. In the study centre, all received questionnaires and lists will be scanned electronically and a TIF-file will be generated to avoid data manipulation. The data will be directly exported in the statistic program (STATA, version 9).

Descriptive statistics: average value with +/- 1 SD and median values of the average blood pressure readings for both groups. In accordance with the normal distribution test it will be decided whether parametric or non-parametric tests are to be applied. Treatment group comparisons for categorical data will be done with the χ^2 ^test. For continuous variables, comparisons between treatment groups were done with *t *tests.

Primary outcome: difference (t2-t0) between the systolic blood pressure average readings from the practice measurement. All patients will be analysed in accordance with the „intention-to-treat” approach and the latest available measurement will be used (last- observation carried forward). When interventions are provided via GPs, one should be aware of a cluster effect. We decided to perform a randomisation on the patient's level since the effect mediated by the GP on the intervention is assumed to be small. Nevertheless, we will account for that and include the factor "Practice" as a random effect in the analysis.

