#### Sample Size

Case number calculation and power analysis were carried out on the basis of the expected effect for systolic blood pressure. With an alpha of 0.05 and a power of 0.9 (one-sided test) this means that 138 patients are required in order to be able to show a clinically relevant blood pressure difference of 7 mm Hg systolic with a standard deviation of 14 mmHg between the groups. Assuming a dropout rate of 20% this means that at least 166 patients are required.

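### The normality-test rule is not lifted for the primary outcome, so the data could select a rank test that carries neither the practice effect nor the 7 mmHg mean difference

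*Protocol article*

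**What the plan says.** All the method statements are in the Analysis section of the protocol article.

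- The general paragraph begins with descriptive statistics for the blood pressure readings and then gives a rule: "In accordance with the normal distribution test it will be decided whether parametric or non-parametric tests are to be applied".
- The same paragraph ends with a sentence that names t tests and attaches no condition. It opens: "For continuous variables, comparisons between treatment groups were done with".
- The next paragraph, on the primary outcome, sets out intention-to-treat with last observation carried forward. It then says that practice will be included "as a random effect in the analysis".

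The Primary end point section makes the outcome continuous: "The difference (t2-t0) between the systolic blood pressure readings at the practice measurement represents the primary end point". The Sample Size section (one-sided alpha 0.05, power 0.9, assumed SD 14 mmHg) states: "138 patients are required in order to be able to show a clinically relevant blood pressure difference of 7 mm Hg systolic".

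No sentence says that the normality rule stops short of the primary outcome, or how a non-parametric branch would take practice into account.

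**The concern.** The primary outcome is a continuous blood pressure variable, so the normality rule covers it as written. If the normality test rejects, the plan points to a non-parametric comparison, and two other commitments fail:

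1. **Practice effect.** A standard two-sample rank test has no term for practice, although the primary-outcome paragraph promises one.
2. **Estimand.** The trial is sized on a difference in means. A rank test does not estimate that difference, so the result could not be set directly against the 7 mmHg called clinically relevant.

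The outcome data would also decide which test is reported. What is at stake is one avoidable degree of freedom in the primary test, and possibly a primary result on a different scale from the one planned.

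**Working it through.** **Step 1: what the sample size assumes.** Inputs from the Sample Size section: difference 7 mmHg, SD 14 mmHg, one-sided alpha 0.05, power 0.90. Assumed: 1:1 allocation. For a two-sample comparison of means,

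n per arm = 2 × SD² × (z₀.₉₅ + z₀.₉₀)² / difference² = 2 × 14² × (1.645 + 1.282)² / 7² = 8 × 8.56 = 68.5, rounded up to 69.

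The total is 138, the plan's own figure. The planned quantity is therefore a mean difference.

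**Step 2: what a rank test would mean for that number.** With truly normal data the rank test has relative efficiency 0.955. The same power would need 138 / 0.955 = 144.5, about 145 patients; at 138 the power is about 0.89. The cost in power is small. The change of estimand matters more.

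**Step 3: would the gate act, and with what effect?** A simulation was run, 4,000 trials per scenario. Assumptions:

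- 35 practices of 4 patients (140 in all), two per arm in each practice; four envelopes per practice is from the Randomisation section.
- Total SD 14; practice intraclass correlation 0, 0.05 or 0.10.
- Errors normal, t with 5 degrees of freedom, or skewed (gamma, shape 2).
- Gate: Shapiro-Wilk at 0.05 in each arm, with the rank test used if either arm fails. The article names no normality test, so this is an assumption.
- The practice model used practice as a fixed effect, standing in for the random effect. No baseline covariate, no dropout.

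Ranges are over the three intraclass correlations (share sent to the rank test: also over both true effects):

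| | Normal | t, 5 df | Skewed |
|---|---|---|---|
| Sent to rank test | 9.4–10.5% | 61.2–70.6% | 99.2–100% |
| Type I error, gated rule | 0.044–0.060 | 0.040–0.050 | 0.038–0.054 |
| Type I error, practice model | 0.050–0.057 | 0.045–0.048 | 0.048–0.051 |
| Power at 7 mmHg, rank test | 0.894–0.898 | 0.943–0.947 | 0.957–0.964 |
| Power at 7 mmHg, practice model | 0.910–0.931 | 0.894–0.926 | 0.898–0.926 |
| Tests disagree, no effect | 2.4–2.7% | 2.8–3.5% | 3.0–3.3% |
| Tests disagree, 7 mmHg | 3.9–4.9% | 5.0–6.5% | 5.2–7.2% |

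Disagreement means that the t test, rank test and practice model do not all give the same significance verdict. It is an upper limit for any one pair.

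**Step 4: reading the table.** The gate is active: even with normal data, about one trial in ten goes to the rank test, as expected from two tests at 5% (1 − 0.95² = 0.0975). The gated rule's highest type I error, 0.060, arose with normal data and no practice effect. The t test, exact in that setting, gave 0.059 on the same simulated data, so the excess is simulation noise (standard error √(0.05 × 0.95 / 4000) = 0.0034). The practice model kept its level and a power of about 0.89 or more for all three shapes, so the mean comparison did not need the gate's protection.

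**The case against.** The strongest defence is that the primary-outcome paragraph is specific and the preceding one general. On that reading the practice model is the primary analysis, and the normality rule serves other variables such as the number of diary entries or of practice contacts. This is reasonable and may be what was intended. But the text does not say so, and the general paragraph itself speaks of blood pressure readings.

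It can also be said that the rank test had more power for the heavy-tailed and skewed errors. That is true. The simulated effect was, however, a pure shift, where ranks and means point to the same difference; a real change score need not behave so. Stratified rank tests could take practice into account, and a mean difference can be printed beside a rank p-value, but the article plans neither.

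The model's full specification and the name of the normality test are details that an article may leave to a fuller document. Their absence is not the point here.

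Four stronger readings are tempting and not supported:

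- A reader might infer three rival primary analyses and three p-values. The gate and the t-test sentence read naturally as one rule (t test unless normality fails), and a t test and a linear mixed model of the change target the same mean difference. The real conflict is with the non-parametric branch.
- A reader might infer that the pre-test inflates type I error. The simulation shows no marked inflation.
- A reader might expect carried-forward baselines to fill the data with zero changes. The figure 0.20 × 166 = 33 is only an upper bound: it needs every dropout to occur before the 3-month visit.
- A reader might extend the point to the χ² test for blood pressure control. The normality rule does not bear on that endpoint, and a mixed logistic model with at most four patients per practice is debatable.

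**Conclusion.** The point holds in a limited form. As written, the normality rule reaches the primary outcome, and its non-parametric branch cannot be reconciled with the promised practice random effect or with the mean difference on which the 138 patients rest. The harm is an avoidable, data-dependent choice of test and a possible loss of the planned estimand.

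The size is modest. Under the assumptions above, the candidate tests differ on significance in about 2–4% of trials with no effect and 4–7% with a true 7 mmHg effect, while type I error stays near nominal. How often the gate would fire depends on the unknown shape of the change scores: from about one trial in ten to nearly all. The conflict between the statements does not depend on the simulation.

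**What to change.** State in the Analysis section that the normality rule does not apply to the primary outcome, and name one primary analysis. This would be a linear mixed model for systolic pressure at t2, or its change from t0, with treatment and baseline systolic pressure as fixed effects and practice as random effect. With baseline in the model, the treatment coefficient is the same for either choice of outcome, so the primary end point keeps its meaning. Report the adjusted mean difference and its confidence interval whatever the distribution. A rank-based or bootstrap analysis may be kept as a labelled sensitivity analysis, and the normality rule may stay for other variables.

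The cost is analysis wording only. Baseline pressure is already measured at t0, and this point gives no reason to change the 138: the simulated one-sided power of the practice model with normal errors was 0.91–0.93 at 140 patients, without the baseline covariate.

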### Exclusion criteria

• Blood pressure reading over 180 mmHg systolic and/or 110 mmHg diastolic.

• Serious general or psychological illness (malignant tumours, serious depressive episodes or evidence of dementia).

• Insufficient knowledge of the German language for instruction and blood pressure recording with a booklet.

All patients will be asked consecutively about participating in the study and they will be handed an information sheet. All patients who have been approached will be included in a list containing the blood pressure booklet code which will be passed on to the study centre. The list remains in the practice so that the study leaders only have anonymous access to the patient data. However, in the practice it is possible to link the blood pressure record book with the medical file of the patient so that all the clinical data is available. Any patients who have been approached and have declined to participate will be included in a list in order to carry out a non-responder analysis of patients with regard to socio-demographic and clinical data.

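### The only test named for blood pressure control under 140/90 is an unadjusted chi-square test; using the t0 pressure already recorded would add a few points of power at no cost

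*Protocol article*

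**What the plan says.** The protocol's Secondary end point section lists "Number of patients, who achieve blood pressure control under 140/90 mm Hg", a yes/no outcome per patient. The Analysis section gives one rule for such outcomes: "Treatment group comparisons for categorical data will be done with" the chi-square test. It names no covariate or stratum.

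Baseline pressure is recorded in every patient. The Primary end point section says: "There will be blood pressure measurements by the general practitioner at the start (t0) as well as after 3 months (t1") and again at 6 months (t2). The entry range is wide. The inclusion criteria set the lower limit ("both measurements must be greater that 140/90 mmHg with the second measurement qualifying for inclusion") and the exclusion criteria the upper one ("Blood pressure reading over 180 mmHg systolic and/or 110 mmHg diastolic").

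On practice, the paragraph of the Analysis section that opens with the primary outcome closes with: "Nevertheless, we will account for that and include the factor 'Practice' as a random effect in the analysis". It does not say whether this extends to the control end point.

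**The concern.** A patient who enters at 142 mmHg and one who enters at 178 mmHg have different chances of finishing below 140, if t0 predicts t2 at all. The chi-square test treats them alike. The primary end point uses t0 through the difference t2-t0; the control end point, as planned, does not use it.

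What is at stake is precision. The trial is sized for the systolic difference only, and a yes/no cut of the same reading carries less information, so this end point starts with less power than the primary one. It is also the result a clinician reads most easily: how many patients were brought under control.

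**Working it through.** **Inputs from the protocol.** Effect 7 mmHg systolic, SD 14 mmHg, one-sided alpha 0.05, power 0.90, 138 patients (Sample Size); entry above 140 and up to 180 mmHg systolic; control cut at 140; four envelopes per practice (Randomisation). **Assumed, because the protocol does not give them:** 1:1 allocation, t0-t2 correlation, mean t2 pressure, intraclass correlation (ICC) for practice. All power figures cover only the systolic half of 140/90.

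**1. The plan's own figure.** n per arm = 2(1.645 + 1.282)² × 14² / 7² = 68.5, so 69 per arm and 138 in total. The stated number reproduces.

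**2. Power of the chi-square test for control.** Take t2 systolic pressure as normal with SD 14 and mean 145 (control) or 138 (intervention). The control rates are Φ((140 − 145)/14) = 0.360 and Φ((140 − 138)/14) = 0.557. With 69 per arm, power is 0.753 one-sided and 0.641 two-sided. At control-arm means of 140 and 150, two-sided power is 0.632 and 0.607.

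**3. Gain from t0 systolic pressure, t2 SD fixed at 14.** Simulated trials of 138 patients with control-arm mean 145 and no practice effect (2,500 per row; 6,000 for correlation 0.4). Each cell gives power with chi-square, then with logistic regression on arm and t0 systolic pressure.

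| t0-t2 correlation | one-sided | two-sided |
|---|---|---|
| 0 | 0.766 to 0.757 | 0.643 to 0.640 |
| 0.3 | 0.755 to 0.765 | 0.629 to 0.657 |
| 0.4 | 0.758 to 0.790 | 0.638 to 0.684 |
| 0.5 | 0.748 to 0.802 | 0.629 to 0.704 |
| 0.7 | 0.725 to 0.867 | 0.612 to 0.784 |

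The one-sided gains are about 0, 1, 3, 5 and 14 points. The two-sided gains are about 0, 3, 5, 8 and 17 points.

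**4. A second model.** Usual systolic pressure N(148, 14), entry readings above 140 to 180, a control-arm fall of 5 or 10 mmHg, 3,000 trials per setting. The within-person SD sets both correlation and spread.

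| within-person SD | t2 SD | SD of change | one-sided power, chi-square to adjusted (fall 5; fall 10) |
|---|---|---|---|
| 6 | 11.5 | 8.3 | 0.881 to 0.953; 0.891 to 0.966 |
| 8 | 12.9 | 10.9 | 0.792 to 0.858; 0.817 to 0.875 |
| 10 | 14.5 | 13.3 | 0.713 to 0.771; 0.739 to 0.781 |

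Only the last row is near 14 on both measures of spread, which matters because the protocol does not say whether its SD is of readings or of change. The correlation there is 0.46 and the gains are 5.8 and 4.2 points. A repeat with 6,000 trials gave 0.708 to 0.757 and 0.734 to 0.777 one-sided (4.9 and 4.3 points), and 0.587 to 0.648 and 0.611 to 0.672 two-sided (6.1 points each).

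**5. Validity.** With no effect, over correlations 0 to 0.7 and ICC 0 to 0.10, the two-sided rejection rate was 4.1% to 5.0% for chi-square and 3.9% to 5.1% for the adjusted model. Neither inflates the false-positive rate.

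**6. Practice.** Adding practice to the baseline-adjusted analysis gave about 0 to 3 further points two-sided at ICC 0 to 0.10. At correlation 0.5, for example, 0.712 became 0.741 at ICC 0.10. Practice entered as fixed effects in a linear model for the yes/no outcome, as a stand-in for the random effect.

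**The case against.** The best defence is that nothing here is wrong. The test is prespecified and keeps its false-positive rate, the end point is secondary, and a journal article may leave covariates to a fuller analysis plan. The chi-square sentence is also generic: it stands in the paragraph on descriptive statistics and does not name the control end point. This limits the point to an optional improvement. It does not remove it, because the article does name a test, and control under 140/90 is a categorical outcome to which that rule naturally applies.

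A reader might infer more in three ways that the documents do not support.

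- **That practice is ignored, or that the plan contradicts itself.** The Analysis section promises to "include the factor 'Practice' as a random effect in the analysis". If that covers only the primary outcome, nothing conflicts. If it covers every end point, practice is not ignored, but chi-square cannot be the whole analysis. Only the scope is unclear.
- **That chance baseline imbalance undermines the chi-square result.** Under randomisation the significance level already allows for it, as step 5 confirms.
- **That power rises from about 89% to 97%.** Those figures need less variation than the protocol's SD of 14 mmHg. They are also one-sided, and the protocol states one-sided testing only for the systolic sample size ("With an alpha of 0.05 and a power of 0.9 (one-sided test"). A chi-square comparison is ordinarily two-sided.

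It is also fair to say that the full model proposed was not simulated: diastolic pressure and a random effect in a logistic model with about four patients per practice were not tested.

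**Conclusion.** The point holds as a free improvement to one secondary end point. The named analysis of control is valid but leaves recorded baseline information unused. At the protocol's effect, sample size and approximate SD, adjustment for t0 systolic pressure is worth about 3 to 6 points of power one-sided, or about 5 to 8 two-sided, if the t0-t2 correlation is about 0.4 to 0.5. Over the wider range examined, the two-sided gain runs from about nil at correlation 0 to 17 to 19 points at 0.7 (ICC 0 to 0.10). No correlation is given, so the exact gain cannot be fixed from the protocol. Nearly all of it comes from baseline pressure and little from practice. The primary analysis and the false-positive rate are not affected.

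**What to change.** In the Analysis section, state that control under 140/90 at t2 will be analysed by logistic regression on arm, t0 systolic pressure and t0 diastolic pressure. Report the adjusted odds ratio together with a standardised risk difference, because the adjusted odds ratio is conditional on baseline and does not show directly how many more patients were brought under control. Keep the chi-square comparison as a descriptive line.

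Add one sentence on whether the practice random effect applies to this end point. If it does, it belongs in the logistic model; with about four patients per practice, name a fallback in case that model does not converge.

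The cost is a change of wording, made before outcome data are seen by arm so that the adjustment is prespecified. It needs no new measurement and no change to patient procedures or sample size.
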